## Materials/Design

### Objectives

Our primary goal is to evaluate the effectiveness of pharmacist plus health promoter support (*Pharmacist+HP*) compared with pharmacist alone (*Pharmacist*) on diabetes behaviors (including healthy eating, physical activity, and medication adherence), hemoglobin A1c, blood pressure, and LDL-cholesterol levels among African-American and Latino adults with uncontrolled type 2 diabetes. Secondarily, we will evaluate the maintenance of improved diabetes behaviors, as well as clinical outcomes, by phasing out health promoter support from the *Pharmacist+HP* group after one year. Also, we will evaluate the intensification offered by adding a health promoter after one year of Pharmacist alone. Finally, we will determine the cost and cost-effectiveness of the *Pharmacist+HP* and *Pharmacist* alone approaches.

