### Sample size calculation

Sample size calculations are powered to detect change in A1c. Based on a previous study [31], we estimated a mean baseline A1c level of 10.0% with standard deviation of 1.8% and an effect size of (1.0/1.8) 0.56. The cross-time correlation was estimated to be 0.30. We adjusted for clustering, assuming an intraclass correlation coefficient (ICC) of 0.02 and cluster size of 30, which yields a design effect of 1.58. Two-sided alpha of 0.05 and 80% power are assumed requiring a minimum of 114 per group. Allowing for an estimated 10% drop-out during each of the two years, approximately 150 patients will be required for each group (or 300 total).

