### Data analyses

Data will be analyzed for clinical effectiveness using intention-to-treat principles [32-34]. To represent dropouts in the analysis, missing data will be imputed using various approaches, such as “last value carried forward.” The Little and Yau “return to baseline” imputation rule, in which any gains over baseline levels dissipate upon dropout, will be used for primary analyses. Patients who share a single primary care physician (PCP) or health promoter (HP), might exhibit similarities that are not shared with patients attended to by other physicians. To address this, we will include random effects in the model for clinic site, PCP, and HP. We will include as predictors relevant care and treatment-related variability such as medication therapy intensifications and clinical encounter frequency.

We will test the hypothesis that A1c, blood pressure, and LDL-cholesterol levels will be lower and diabetes behaviors (including medication adherence) will be improved with patients receiving *Pharmacist+HP* compared with those receiving *Pharmacist* alone. Univariate comparisons between the two study groups with respect to outcome measures and covariates at baseline will be conducted using Chi-square tests for categorical variables, Kruskal-Wallis tests for ordinal variables, and linear mixed models for continuous variables. Non-normal continuous data will be transformed prior to linear model analyses. The baseline variables include demographic, therapy complexity, and health literacy data. If we find any between-group differences at baseline, we will adjust for this in our primary multivariate analyses by including relevant covariates.

We will also extend the usual analysis of crossover designs by including a longitudinal trend component in the first year. Thus, we can examine the time course (0, 6, and 12 months) as linear or quadratic over the first three measurements. This will allow us to investigate whether changes are made early, and at what rate they continue through the rest of the time period. This analysis permits the comparison of trends between *Pharmacist* and *Pharmacist+HP* conditions. In addition, we will regard participants as a random effect and will use Gaussian mixed-model estimations (SPSS MIXED command). We can then substitute treatment by period interactions for the carry-over effects, and the model can be reduced in a recommended sequence (first omit carry-over, then omit treatment, finally omit period).

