The primary analysis of each outcome in the repeated measures design will be conducted in a general linear mixed model framework. In addition, SPSS MANOVA (for repeated measures) will be used to explore the simultaneous impact of the treatment on multiple correlated dependent variables, including the use of Roy-Bargmann stepdown F-tests and discriminant function analysis as post hoc tests to identify subsets of outcome measures affected [35]. SPSS MIXED will be used to explore patterned covariance structures such as compound symmetry and autoregression along with incorporating time-varying covariates, such as depression. MANOVA secondary analyses will explore the impact on results of inhomogeneous baseline variables. Exploratory subgroup analyses will determine which participants in the intervention group had the greatest improvement in outcomes, based on demographic factors, health literacy, and medication regimen. Group by time-trend interaction contrasts also will be used to explore different group trajectories of change. In addition, we will investigate the potential consequences of medication intensification (e.g., initiation of insulin) by evaluating changes in body mass index and severe hypoglycemia.

We will explore diabetes-related behaviors (including eating habits, physical activity, and medication adherence) as well as medication treatment intensification as alternative mediators using MPlus [36]. We will also test the hypothesis that diabetes behaviors and clinical outcomes will be maintained one year after phase-out of HP support. Finally, we will test the hypothesis that diabetes behaviors and clinical outcomes improved by adding HP support after one year of *Pharmacist* alone.

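### Maintenance after health promoter phase-out is framed as a hypothesis to test, but the stated tests of difference can only reject no change and cannot support it

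*Protocol article*

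**What the plan says.** The Objectives section of the protocol article makes maintenance a secondary aim: "Secondarily, we will evaluate the maintenance of improved diabetes behaviors, as well as clinical outcomes, by phasing out health promoter support". The last paragraph of Data analyses turns it into a test: "We will also test the hypothesis that diabetes behaviors and clinical outcomes will be maintained one year after phase-out of HP support".

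The models described in Data analyses are general linear mixed models, a crossover model with carry-over or treatment-by-period terms, group-by-time trend contrasts, and repeated-measures MANOVA. For dropouts, the same section lists last value carried forward and names a return-to-baseline rule, "in which any gains over baseline levels dissipate upon dropout, will be used for primary analyses".

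The sample size was set for a different question: "Sample size calculations are powered to detect change in A1c".

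**The concern.** The article's other hypotheses are directional: outcomes better in one arm, or improved after a health promoter is added. A test of difference can support those. Maintenance is a claim of no important loss, and a test of difference cannot support that. A non-significant change is compatible with a real loss, and the noisier the data, the easier non-significance is to obtain.

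At stake is whether health promoter support can be withdrawn without losing what was gained. That question is the reason for the second year in the Pharmacist+HP arm. If the report rests on a p-value, a relevant rise in A1c could be presented as maintenance. The dropout rule adds a second problem, because the two imputation rules named would move this contrast in opposite directions.

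**Working it through.** **Inputs (Sample size calculation).**
- Spread and planned effect: "standard deviation of 1.8% and an effect size of (1.0/1.8) 0.56".
- Correlation between visits: 0.30.
- Clustering: ICC 0.02 with clusters of 30, so the design effect is 1 + 29 × 0.02 = 1.58.
- Error rates and resulting size: "Two-sided alpha of 0.05 and 80% power are assumed requiring a minimum of 114 per group".
- Dropout: 10% in each of two years from 150 per arm, so 150 × 0.9 × 0.9 = 121.5, taken as 121 completers.

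**Reproducing the plan's figure.**
- SD of a change = 1.8 × √(2 × (1 − 0.30)) = 2.13.
- n per group = 2 × 2.13² × (1.96 + 0.842)² / 1.0² = 71.2, rounded up to 72.
- 72 × 1.58 = 113.8, i.e. 114, as stated.

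So the plan itself works with a change-score SD of 2.13, and its 1.0 point is a between-group difference.

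**Precision of the 12-to-24-month change in the Pharmacist+HP arm.** SE = 2.13 × √(DE/121), where DE is the design effect. The chance that a true rise δ is non-significant is Φ(1.96 − δ/SE).

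| | DE = 1 | DE = 1.58 |
|---|---|---|
| SE | 0.194 | 0.243 |
| 95% CI half-width | 0.38 | 0.48 |
| Non-significant, true rise 0.5 | 27% | 46% |
| Non-significant, true rise 0.3 | 66% | 77% |

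With the design effect, an observed rise just under 0.48 would be non-significant, yet its upper 95% limit would be about 0.95 point.

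**Sensitivity to the correlation.** The plan gives a single value, 0.30. The other two are assumptions.

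| Correlation | SD of change | Non-significant at a true rise of 0.5: DE = 1 | DE = 1.58 |
|---|---|---|---|
| 0.30 | 2.13 | 27% | 46% |
| 0.5 | 1.80 | 14% | 32% |
| 0.7 | 1.39 | 2% | 12% |

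**Effect of return-to-baseline, if used here.** Year-1 dropouts sit at baseline at both visits and contribute zero change. Year-2 dropouts are 0.9 × 0.1 = 9% of the arm, and each is given a loss equal to the whole 12-month gain G. With no true loss, the built-in loss is 0.09 × G. The documents do not give G; assuming 1.0 to 2.0 it is 0.09 to 0.18 point.

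A simulation of all 150 patients under this rule, with correlation 0.30 and a true rise of 0.5 among those who stay, gave non-significance in about 7% to 15% of trials without the design effect and 21% to 34% with it. Part of that fall comes from a smaller SE, because all 150 are counted and year-1 dropouts add no variation.

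Last value carried forward would instead give year-2 dropouts zero loss.

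**Power of a margin-based claim.** With an illustrative margin of 0.5 point, no true loss and the upper 95% limit required to lie below the margin, power = Φ(0.5/SE − 1.96) = 73% (DE = 1) or 54% (DE = 1.58). With the unrounded 121.5 completers the first figure is 73.5%. Reaching 80% would need 143 or 226 patients in the arm.

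**The case against.** The strongest reply is that this is a condensed article, and a margin, reference visit or decision rule for a secondary aim is normally left to the full protocol or SAP. That stands as far as the missing margin goes, and its absence is not the point here. The point is that the article states a hypothesis in a form that the methods it names cannot confirm.

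A reader might infer that the investigators will treat a non-significant change as maintenance. Nothing in the article says so; the risk is only that such a result could be misread.

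A reader might also infer that a 0.5-point rise means half the planned effect has been lost. The documents do not support that: 1.0 point is a between-group difference, and the within-arm gain at 12 months is not given.

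Nor does the plan simply make maintenance too easy to declare. Return-to-baseline works against it, and since the rule is assigned to primary analyses, it is unclear whether it covers this secondary aim at all.

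*Maintained* could instead mean still better than baseline at 24 months, which a significant result would support. That reading could be satisfied after much of the gain had gone, and because only health promoter support is phased out, it would not isolate the benefit of that support.

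The crossover model does address persistence through its carry-over term, but that is again a test of difference, and it is the first term removed when the model is reduced.

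**Conclusion.** The concern holds in a limited form. The stated tests cannot support the maintenance hypothesis, whatever the correlation or dropout rule. How often a true 0.5-point rise would go undetected does depend on them: 27% or 46% among completers at correlation 0.30 (without or with the design effect), 14% or 32% at 0.5, and 2% or 12% at 0.7. If return-to-baseline were applied, the bias would run against maintenance, by about 0.09 to 0.18 point on an assumed gain of 1.0 to 2.0.

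These figures assume a normal approximation and equal SDs at the two visits. Applying the plan's design effect to a within-arm change is also an assumption, so both versions are shown. The aim is secondary, so this is a moderate point, but the correction is cheap.

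**What to change.** In the last paragraph of Data analyses, replace the test of maintenance with estimation: the 12-to-24-month change in the Pharmacist+HP arm with its 95% confidence interval, from the likelihood-based mixed model fitted to observed data. Give return-to-baseline and last value carried forward as sensitivity analyses. They matter because the observed-data estimate would favour maintenance if patients who relapse tend to leave in a way that their recorded values do not predict.

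Claim maintenance only if the interval excludes a loss margin fixed in advance; 0.5 A1c point is used above purely as an illustration. For any outcome without an agreed margin, report the interval descriptively. State that maintenance will not be inferred from a non-significant change.

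The cost is wording and one contrast, with no change to visits or data collection. The downside is that a formal claim becomes harder: power is about 54% to 74% for a 0.5-point margin with no true loss, and the plan should say so.

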### Pharmacists

Pharmacists will provide medication and disease management services to patients following an established Pharmacist Management Protocol. In providing care, pharmacist disease management services are comparable to other disease management programs and include comprehensive needs assessments, proactive health promotion, patient-centric goals and education, interventions to encourage behavioral change, and PCP support and feedback [37]. The pharmacists will review current medication use, identify therapeutic goals (particularly A1c, blood pressure, and LDL cholesterol), formulate a PCP-approved plan of care, and document the plan in the EMR. Pharmacists will educate and encourage lifestyle changes based upon ADA nutrition and physical activity guidelines [38,39]. All patients recruited into this study will require medication to control their diabetes. The PCPs and pharmacists will decide on the algorithm and approach to intensify therapy and how medication changes may be made (based on national guidelines) [40-42]. The intention is to establish optimal communication with minimal PCP burden (a similar approach to our pilot study). Individual goals will be identified for each participant for A1c, blood pressure, and LDL-cholesterol (e.g., A1c ≤ 7%, blood pressure < 130/80 mm Hg, and LDL < 100 mg/dL). In the proposed study, pharmacists will adopt the ADA approach to individualized care, where the general goal for non-pregnant adults is A1c less than 7%. The pharmacists may decide upon less stringent goals for those with a history of severe hypoglycemia, limited life expectancy, advanced micro- or macrovascular disease, or extensive comorbid conditions [43].

Initially, the pharmacists will meet with patients to reconcile medications and discuss therapeutic goals. Next, the pharmacists will assess common barriers to medication adherence including poor memory, lack of diabetes knowledge, health beliefs, cost, medication burden, physical disabilities, and social barriers. Following the initial visit, encounters may occur in person, at the clinic, or by phone. Duration between encounters may increase based on individual preference and when participants reach goals (with maximum of three months). The pharmacist activities will include an evaluation of adherence, medication reconciliation, and review of home glucose and/or blood pressure monitoring log data. Pharmacist education of patients will target medication (name and purpose of medications; time, strength, and method of administration); drug interactions and side effects; goals of therapy; basic lifestyle modifications; and use of pillbox, low-literacy medication lists, or other adherence aids.

Pharmacists will adjust therapy according to the plan of care under PCP guidance and notify PCPs of agreed-upon modifications via the EMR. Side effects identified by the HP or pharmacist will be conveyed to the PCP immediately and if the PCP is not available, the covering clinic physician will be contacted per Pharmacist Management Protocol. Laboratory assessments including electrolytes and renal function will be completed per medication titration protocol. In addition to scheduled study-related clinical data collection, point of care testing will be performed during pharmacist visits as needed based on guidelines to further guide treatment plans. For hypoglycemia, pharmacists routinely monitor hypoglycemic events, address prevention and review treatment. This includes three steps: (1) addressing hypoglycemia with every patient contact; (2) applying principles of aggressive therapy (education, empowerment, frequent glucose self-monitoring, flexible medication regimen, individualized goals, professional guidance); and (3) considering risk factors for hypoglycemia [44].

PCPs and clinical pharmacists are located in the same medical center building. The pharmacists have direct access to the PCP and routinely communicate in person, by telephone, and by EMR messaging depending on urgency. The pharmacist may adjust the medication regimen and provider refills in accordance to the PCP-directed care plan and response to therapy (to optimize blood glucose, blood pressure, and cholesterol levels). All adjustments, refills, and testing are completed under guidance of the participants’ providers and updated in the EMR medication list. Pharmacists have access to participants’ full medical records and can review flow-sheet and other chart data including blood test results, clinical progress notes, problem and medications lists, drug allergies, hospitalization records, and emergency room reports. Pharmacists will forward all electronic progress notes to the PCP EMR “Inbox” when medication changes are made. Progress notes include a detailed list of medications, estimated adherence levels, and home glucose and blood pressure monitoring log information. However, for urgent medical reasons, the PCP or covering provider will be contacted. If, for any reason, the PCP feels that the patient should not remain in the study, the provider can inform the PIs to disenroll the participant.

### Health promoters (HPs)

Health promoters conduct patient encounters, provide medication and lifestyle adherence support and communicate with pharmacists. Each clinical site will work with English- and Spanish-speaking health promoters (HPs) who are each responsible for up to 25 participants. Candidates for HP positions will be identified through advertisements, announcements, and organization meetings targeting these contacts. HPs will have: (1) U.S. citizenship; (2) a vehicle for transportation; (3) a bachelor’s degree; and (4) excellent communication skills. HPs will represent the communities being served.

All HPs will receive standardized training/re-training via two educational curricula: (1) the *Diabetes Empowerment Education Program* (DEEP) [45]; and (2) *Training Curriculum for Health Coaches*[46]. DEEP uses an empowerment/autonomy framework. In addition, it includes adult learning methodologies and interactive group exercises with role-playing. The program trains HPs in increasing patients’ knowledge, skills, and autonomy related to diabetes management and control. The training addresses physical activity, nutrition, psychosocial support, medication use, and the health care team interaction. The *Training Curriculum for Health Coaches*, includes sessions on the collaborative paradigm (*ask* instead of *tell*), action plans, problem solving, cardiovascular disease and medication management. HPs will also observe and shadow pharmacists’ interactions with patients in the UIMC Medication Therapy Management (MTM) Clinic as an apprenticeship to gain insight into clinical pharmacists’ roles and activities, such as medication reconciliation. Following training, we will assess HP competencies in counseling and diabetes-related clinical skills. HPs are video-recorded with standardized patients to provide evaluation and feedback on coaching and empowerment activities.

In addition, health promoter training will include time to orient HPs to resources available to patients in the medical facility (e.g., on-site pharmacy and social workers). There will be time allocated for the HPs to tour the medical campus to gain familiarity of the various clinical sites where they could meet with participants individually or jointly with pharmacists. Other training experiences include didactic sessions with a certified dietician (with trips to a grocery store to review food labels and compare products), clinical observations of health care providers counseling on medication use, and independent learning through video and computer multimedia. Periodic educational sessions are provided by specialists from the medical center.

HP encounters will include home visits and telephone contact. By performing home visits, the HPs may evaluate home issues related to lifestyle changes (e.g., food inventory), medication adherence (e.g., medication storage), and technique of injecting insulin and testing blood sugar. In addition, the HPs will have glucose meters and automated blood pressure home measurement devices to check blood pressure and blood sugar. The HP encounter documentation will include duration of encounter, topics of discussion, medications addressed, and need for pharmacist communication. The HPs and pharmacists will communicate in-person, by phone, or by secure e-mail to discuss participant issues.

HPs will attend to medication adherence-related issues by identifying barriers, solving problems, and providing autonomy support. For example, HPs will address language barriers with providers, limited health literacy, transportation barriers, and cultural barriers (e.g., alternative therapy use that may interfere with or replace the use of conventional medicines). HPs will attempt to elicit and address concerns, beliefs, and social norms that may threaten acceptance of and adherence to conventional therapies. The HPs will parallel pharmacist activities by evaluating adherence, assisting in medication reconciliation, reviewing home glucose and blood pressure monitoring data, and providing reinforcement of proper medication use. They will assist in the implementation of pillbox use and other adherence aids as needed. Also, HPs will have an iPad for participant use of multimedia for education, skill building, and motivation (*“Living Well with Diabetes”*) [31].

HPs will also provide education and support that reinforce lifestyle adherence in conjunction with medication adherence. HPs are trained on the diabetic diet along with basic physical activity recommendations so that they can work with patients to set individual goals. Education will address realistic and achievable food choices, portion sizes, cooking preparation, relationships between medications-meals-glucose levels, integration of physical activity into lifestyle, and local community resources for grocery shopping and physical activity.

### Study measures

Control variables will be completed at baseline as follows. *Socio-demographic Data* will include age, gender, self-reported race and ethnicity, country of origin (if other than U.S.), income, highest level of education, current employment status, marital status, number of adults and children at home (and adults with diabetes), global health status [47], and insurance. If the participant is Latino, data will also include language spoken and thought in, provider language spoken, and use of interpreter. *Diabetes and Medical History* will include time since diabetes diagnosis, receipt of diabetes education, home glucose monitoring frequency, and self-reported provider visit frequency. *Health Literacy* will be assessed using three items validated in English and Spanish speaking populations [48]. A *Transportation Survey* will assess barriers to visiting health care providers or a pharmacy to obtain medication refills (currently undergoing validation). *Interpersonal Processes of Care*, including communication and other experiences with doctors and staff members, will be assessed by the Interpersonal Processes of Care Survey: Short Form (IPC-18).

Intermediate variables will be collected at four time points (0, 6-, 12-, and 24-months). *Diabetes Knowledge* will be assessed using the Spoken Knowledge in Low Literacy in Diabetes Scale (SKILL-D) (reliability .72) [49]. *Depression* will be measured using the 2-item Patient Health Questionnaire (PHQ-2). *Social Support* will be measured using a 4-item assessment of amount of total support received and satisfaction of support from family, friends and healthcare team [50]. *Autonomous Self-Regulation* will be measured using 6-item Treatment Self-Regulation Questionnaire (TSRQ, reliability 0.85-0.93) [51,52]. The items begin with the stem, “The reason I would take my diabetes and cholesterol medications exactly as prescribed is…” Responses include ratings of reasons for taking medications, such as, “…because I feel personally satisfied when I keep my diabetes and cholesterol within strict guidelines.” *Perceived Competence* will be measured using the 4-item Perceived Competence Scale (PCS) to assess patients’ experiences of feeling able to manage their diabetes successfully (reliability 0.80-0.94) [51,53,54]. Scores are associated with quality of life, medication adherence, and A1c [51,53].

*HP Activity* will be collected on a standardized worksheet completed after every participant contact (by phone and in-person). Information obtained will include mode, time, and content of contact, results of glucose or blood pressure self-monitoring, goals, and interventions. Additional information collected includes *PCP and Pharmacist Activity and Medication Changes.* The reconciled medication list from the medical chart will be used as data to evaluate medication changes and overall complexity of therapy. Intensification of therapy will be defined as the number of increases in the dosage of an antihypertensive agent, hypoglycemic agent, or insulin, or the addition of a new agent since the baseline visit [21]. Chart review will define the number of PCP and pharmacist encounters as well as the number of pharmacist- or physician-initiated medication changes. Chart review will also include information on actual medications prescribed for diabetes, hypertension and hyperlipidemia, co-morbid conditions, and diabetic complications.

*Clinical Outcomes* will be collected at four time points (0, 6-, 12-, and 24-months). Professional research staff will perform phlebotomy and measure blood pressure, weight and height. These staff will be blinded to participant group assignment. Hemoglobin A1c will be obtained via phlebotomy. The laboratory test has National Glycohemoglobin Standardization Program certification. Fasting lipid profiles will also be obtained via phlebotomy, including HDL, LDL, and triglyceride measurements. Both A1c and lipid profile results will be placed in the participant’s EMR. Height and weight measurements will be obtained to determine body mass index (BMI). A calibrated digital scale will measure weight. A height stadiometer will measure body height, with participants removing their shoes. Blood pressure measurements will be recorded on participants sitting down for at least five minutes, following standard procedure.

*Self-Care Behaviors* related to diabetes self-management including diet and physical activity will be evaluated through the Summary of Diabetes Self-Care Activities Measure (SDSCA) [55]. This includes 11 core items on diet, exercise, blood sugar testing, foot care, and smoking. *Medication Adherence* will be quantified using two methods. The Morisky Medication Adherence Scale will be used to assess self-reported adherence for all participants. The 8-item scale (reliability 0.83) will be completed once for adherence to diabetes medication and once for hypertensive medication, if applicable [56]. The second method of adherence evaluation will consist of obtaining objective pharmacy refill data. Each participant will provide contact information for all of the pharmacies where prescriptions have been filled for the past year. The HIPAA authorization form allows research personnel to contact the pharmacies for fill information. The personnel will contact these pharmacies to collect information on the prescriptions filled. For each prescription, the medication name, date dispensed, dosage, frequency, quantity, and days supply will be requested following an approach similar to that taken in a study on asthma [57]. The Proportion of Days Covered (PDC), a measure of adherence, will be calculated for all diabetes and hypertensive medications using the prescription fill data obtained from pharmacies. *Health Related Quality of Life* will be measured using the Diabetes Distress Scale (DDS4) [58], a 4-item measure of disease specific quality of life.

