### Inclusion criteria

Patients will be eligible for the study if they: (a) are self-identified as Latino/Hispanic or African-American; (b) have verbal fluency in English or Spanish; (c) are age 21 or above; (d) have a history of type 2 diabetes; (e) have an elevated A1c level 8% or higher in the past year (confirmed through EMR); (f) received primary care at UIMC for at least one year; and (g) take at least one oral medication for diabetes or hypertension (for adherence assessment).

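### LDL is an outcome and a treatment target, but the intensification count omits lipid-drug dose increases and both adherence measures omit lipid drugs

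*Protocol article*

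**What the plan says.** **LDL as outcome and target.** Objectives (Protocol article) puts LDL in the primary goal, which covers diabetes behaviors and "hemoglobin A1c, blood pressure, and LDL-cholesterol levels among African-American and Latino adults with uncontrolled type 2 diabetes". Data analyses repeats it: "We will test the hypothesis that A1c, blood pressure, and LDL-cholesterol levels will be lower" with the combined intervention. Under Pharmacists, "Individual goals will be identified for each participant for A1c, blood pressure, and LDL-cholesterol", and the pharmacist may adjust the regimen to improve cholesterol as well as glucose and blood pressure.

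**Medication variables.** Study measures defines intensification as the "number of increases in the dosage of an antihypertensive agent, hypoglycemic agent, or insulin", or a newly added agent since baseline, with no drug class given for the new agent. PDC "will be calculated for all diabetes and hypertensive medications". The Morisky scale is completed once for diabetes medication and, where applicable, once for hypertension medication.

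**Use in analysis.** Data analyses will explore diabetes behaviors, including medication adherence, and "medication treatment intensification as alternative mediators using MPlus". The same section names medication intensification among the predictors in the outcome models. The abstract and the closing Discussion say the design will separate the effects of lifestyle adherence, medication adherence and intensification on clinical outcomes, and they make no exception for LDL.

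**Data collected.** Chart review will record "actual medications prescribed for diabetes, hypertension and hyperlipidemia". Pharmacies will be asked for drug name, dispensing date, dosage, frequency, quantity and days' supply for each prescription.

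**The concern.** The protocol's own rationale is that the intervention works on LDL partly through drugs. The Background says better adherence and intensification should help patients reach cholesterol goals, and the self-regulation questionnaire asks about reasons for taking cholesterol medication. The two constructs meant to carry that pathway are nevertheless defined almost entirely on other drug classes. If Pharmacist+HP lowers LDL because lipid-drug doses go up or lipid drugs are taken more reliably, the stated mediators would register little of it. A weak or null medication pathway for LDL could then be read as evidence that lipid treatment did not matter, when it had barely been measured.

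**Working it through.** **1. Drug classes side by side** (Study measures, Protocol article)

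| Variable | Glucose drugs | Antihypertensives | Lipid drugs |
|---|---|---|---|
| Intensification: dose increase | counted | counted | not counted |
| Intensification: new agent | counted | counted | possible; class not stated |
| PDC | yes | yes | no |
| Morisky | yes | yes, if applicable | no |
| Chart review of drugs prescribed | yes | yes | yes |

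No other section adds lipid drugs to the intensification count or to an adherence measure.

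**2. Size of the distortion in the intensification slope.** The documents give no rates of medication change, so these inputs are assumptions for illustration:
- Counts per patient are independent Poisson, with mean (and so variance) 1.5 for glucose drugs, 1.5 for blood-pressure drugs and 1.0 for lipid drugs.
- The true LDL slope is -15 mg/dL per lipid-drug change.
- A fraction f of lipid-drug changes are new starts, which the definition may count. The remaining 1 - f are dose increases, which it does not count.
- All classes are summed into one count.

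The covariance of LDL with the count is -15 × f. The variance of the count is 1.5 + 1.5 + f = 3 + f. The slope is therefore -15 × f / (3 + f).

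| f | Slope on the count (mg/dL) | Share of -15 |
|---|---|---|
| 0 | 0 | 0% |
| 0.25 | -15 × 0.25/3.25 = -1.2 | 8% |
| 0.5 | -15 × 0.5/3.5 = -2.1 | 14% |
| 0.75 | -15 × 0.75/3.75 = -3.0 | 20% |
| 1 | -15 × 1/4 = -3.75 | 25% |

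Positive correlation between classes would lessen the loss. That is plausible, because the same pharmacists work toward all three goals.

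**3. From slope to mediated effect.** An indirect effect multiplies this slope by the arm difference in the count, so the table is not the share of mediation recovered. Take f = 0.5 and hold the variances at the rates above:
- If the HP arm raises every class in proportion to its rate, the pooled indirect effect is the fraction f of the true one, here 50%.
- If it raises only lipid-drug changes, the share is f × f/(3 + f) = 0.25/3.5 = 7%.
- If it raises glucose and blood-pressure changes by 0.5 each and lipid changes not at all, the pooled estimate is 1.0 × -2.1 = -2.1 mg/dL, although the true lipid-drug pathway is 0.

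The LDL slope is attenuated in every row of step 2. The mediated effect is mismeasured by an amount that depends on how the arms differ by class.

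**4. Adherence.** PDC and Morisky contain no lipid component. They can reflect lipid-drug adherence only as far as it tracks adherence to the other drugs.

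**5. Sample size.** The 114 per group uses A1c inputs only. The SD of change is 1.8 × √(2 × (1 - 0.30)) = 2.13. A difference of 1.0 at two-sided 0.05 and 80% power needs 72 per group, and 72 × 1.58 = 113.8, rounded up to 114. No medication variable enters.

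**The case against.** **The LDL mediation analysis is inferred.** Data analyses calls the mediation work exploratory and names no outcome. This stands and limits the weight of the point. LDL is in scope because it is in the primary goal and hypothesis, and because the abstract and Discussion promise results for clinical outcomes generally.

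**New agents are not class-limited.** This also stands. A reader might infer that the LDL slope is about zero whatever lipid drugs do. The text does not support that, because a newly started lipid drug can score. The supported reading is attenuation, certain for dose increases and for adherence.

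**Lipid changes are captured elsewhere.** Chart review also counts pharmacist- and physician-initiated medication changes without a class limit, and the Discussion says analyses will include medication changes. That shows the data will exist. It does not make that count the definition of intensification, and it does not split it by class.

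**Pooling may not be intended.** The text gives one definition and no outcome-specific version, but does not say how it enters each model. Scoring detail of that kind can sit in an analysis plan. The omission of lipid dose increases is different, because it is in the stated definition.

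**Two further readings are tempting and should not be drawn.**
- One is that pooling necessarily dilutes mediation for A1c and blood pressure. Pooling halves the A1c slope when the two counts are independent with equal variance. If the HP arm raises both classes equally, however, it also doubles the arm difference and the product is unchanged.
- The other is that an all-drug PDC, which would include insulin, conflicts with the criterion that patients "take at least one oral medication for diabetes or hypertension (for adherence assessment". That is an eligibility floor and does not restrict PDC to oral drugs.

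**Conclusion.** The point holds in a limited form. As defined, the intensification count omits lipid-drug dose increases, and neither adherence measure covers lipid drugs, although LDL is an outcome and a treatment target. In an exploratory LDL mediation analysis, or where intensification is a predictor of LDL, the medication variables would mostly describe glucose and blood-pressure drugs. Under the illustrative rates, with independent classes and a pooled count, the LDL slope on intensification is 0 to 25% of the slope on lipid-drug changes. These rates are not the trial's, and correlation between classes would reduce the loss.

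A reader might infer that the LDL treatment effect itself is biased. The definition does not in itself affect the randomized comparison on LDL or the sample size. Whether a post-randomization variable belongs in the outcome model is a separate matter. What is at risk is the interpretation of how LDL changed. That justifies correcting the definition but does not threaten the trial's main result.

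**What to change.** - Add dose increases of lipid-lowering drugs to the intensification definition, and state that new lipid-lowering agents count.
- Score intensification by drug class and use the lipid count in LDL models, both as mediator and as predictor.
- Compute a lipid-lowering PDC from the same pharmacy fill records and use it as the drug-adherence measure for LDL.
- If this is not done, limit conclusions about medication mediation to A1c and blood pressure, and say that the LDL medication pathway was not adequately measured.

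The cost is a small amount of extra coding. Chart review already records drugs for hyperlipidemia and fill details are requested for each prescription, so no visits, patients or changes in care are needed.
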